### Authorised rescue medication

During whole study up to two inflammatory relapses (unilateral or bilateral) will be allowed, one during the first period (baseline–week 16: ACC relapse) and one during the second period (week 16–week 52: any location), before declaring the lack of response to the assigned medication. Based on the location and severity of the relapse, a protocolised rescue treatment with Topical AND/OR Local OR Oral GCs will be allowed. In case inflammation cannot be suppressed in 4 weeks, or a new relapse takes place after 4 weeks, it will be declared treatment failure and the subject will exit the study.

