## Methods and analysis

### Study overview

The Combination THerapy with mEthotrexate and adalImumAb for uveitis (CoTHEIA) study is a phase III, multicentre, prospective, randomised, single-blinded with masked outcome assessment, parallel three arms with 1:1:1 allocation, active-controlled, superiority study design, comparing the efficacy, safety and cost-effectiveness of MTX, ADA or their combination in non-infectious non-anterior uveitis. The duration of the treatment and follow-up will last up to 52 weeks. A 70-day follow-up clinic visit or phone call will take place to assess safety after the last study drug dose. Figure 1 provides an overview of the study timeline and interventions.

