### Recruitment

It will extend over 18 months. The participating study sites attends several 10s of new patients every year, with several hundreds or thousands being followed-up, and many of these sites act as reference centres for other secondary and tertiary hospitals. Candidate subjects will be identified from patients lists AND/OR research databases AND among the new patients attended at the sites.

Subject will not receive any financial compensation for participating in the study.

To ensure subject’s retention during follow-up, we will request contact details, carry out reminder phone calls/send emails, review barriers to attend appointments, and educate them in the significance of research follow-up even if they decide to discontinue the study drugs.

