### Study procedures

Study visits will be the baseline visit, visits at weeks 1, 4, and every 4 weeks thereafter until (a) the subject is determined as unable to achieve complete resolution of the ocular inflammatory process by week 16, OR; (b) the subject is determined as unable to maintain a complete resolution of the ocular inflammatory process, between weeks 16 and 52 OR; (c) the subject completes 52 weeks of this clinical trial, OR; (d) the study is stopped due to the findings of the Data Security Monitoring Board, OR and (e) the subject meets any of the study finalisation criteria.

Informed consent has to be acquired before carrying out any study procedure, including screening tests (online supplemental file 1 contains a sample informed consent). Before baseline (when the subject is randomised), several screening visits can take place up to 14 days before that visit, in order to obtain all the required complementary tests to assess eligibility. The visit window for all scheduled visits is ±3 days through week 4 and ±7 days for all visits following the week 4 study visit. Table 3 provides an overview of the study activities.

10.1136/bmjopen-2021-051378.supp1Supplementary data

**Table 3 T3:** Study activities

Activity	Screening	Baseline	w1	w4	w8	w12	w16	w20	w24	w28	w32	w36	w40	w44	w48	FET	Relapse	Unsch.	70-day follow-up
Informed consent	X																		
Inclusion/exclusion criteria	X	X																	
Medical/surgical history	X	X																	
History of tobacco and alcohol use	X	X																	
Uveitis history	X	X																	
Vital signs/weight/height	X	X														X	(X)		
Physical exam	X	X														X	(X)		
Symptom directed physical exam			X	X	X	X	X	X	X	X	X	X	X	X	X		X		
Chest X-ray	X															X*			
Cerebral MRI†	(X)																		
TB screening	X																		
Serum pregnancy test††	X	X	X	X	X	X	X	X	X	X	X	X	X	X	X	X			
Hepatitis B/C screening	X																		
Syphilis testing (FTA)	X																		
Randomisation		X																	
Best-corrected visual acuity testing	(X)‡	(X)‡		X	X	X	X	X	X	X	X	X	X	X	X	X	X		
Tonometry	(X)‡	(X)‡		X	X	X	X	X	X	X	X	X	X	X	X	X	X		
Slit lamp exam	(X)‡	(X)‡		X	X	X	X	X	X	X	X	X	X	X	X	X	X		
Dilated indirect ophthalmoscopy	(X)‡	(X)‡		X	X	X	X	X	X	X	X	X	X	X	X	X	X		
Fundus photography	(X)‡	(X)‡					X									X	X		
Optical coherence tomography	(X)‡	(X)‡		X	X	X	X	X	X	X	X	X	X	X	X	X	X		
EuroQol-5D	(X)‡	(X)‡		X	X	X	X	X	X	X	X	X	X	X	X	X	X		

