Active chorioretinal lesions; active retinal vascular lesions; macular oedema; ACC; vitreous haze and loss of CVA secondary to inflammation at baseline, week 16, week 52 and relapse visit	MHT, stratified by NIU location. If p-value<0.05, pairwise comparisons using MHT stratified by NIU location will be carried out with Bonferroni adjustment of the pairwise p-values
The time to inflammatory relapse between groups, defined as the time from visit 16 weeks until end of the study, loss of follow-up or appearance of at least one ocular inflammatory manifestation, in those individuals achieving a Good Clinical Response by visit 16 week	Time to relapse between arms will be analysed using log-rank test at a two-sided significance level of 5%. Dropouts due to reasons other than inability to maintain a Good Clinical Response will be considered as censored observations at the time of dropping out. Only subjects able to achieve a Good Clinical Response by visit week 16 will be analysed. We will consider both the time until the onset of the first inflammatory manifestation, each inflammatory manifestation, the first inflammatory manifestation that does not resolve in the following 4 weeks and each inflammatory manifestation that does not resolve in the following 4 weeks.
Best-corrected visual acuity during follow-up	GEE models
Assessment of anti-ADA antibodies (AAA) at weeks 15, 27, 51 and relapse	MHT, stratified by NIU location. If p-value<0.05, pairwise comparisons using MHT stratified by NIU location will be carried out with Bonferroni adjustment of the pairwise p-values
Direct and indirect cost, and incremental cost effectiveness ratios	Cost utility and cost-effectiveness analysis from the perspectives of the National Health System and the Society will be performed. EQ5D scores will derive utility values representing health related quality of life. QALYs will be calculated by the area under the curve assuming a linear evolution of EQ5D values between visits. The average number of QALYs per patient will be calculated for each study arms. Effectiveness will be defined using our primary efficacy outcome. An average cost per patient will be calculated for each study arm, including direct (drug cost, outpatient and inpatient care and other medical cost) and indirect cost (home care, productivity loss): Incremental cost-effectiveness ratios will be calculated, using the MTX monotherapy arm as comparison

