#### Planned methods of statistical analysis for safety-related aims

The safety analysis will be performed in the safety set. Treatment-emergent AEs (events with an onset date on or after the first study drug administration until 70 days following the last study drug administration) will be summarised by treatment group using descriptive statistics. SAEs with onset after informed consent but before the first study drug administration will be considered as pretreatment SAEs and reported separately.

AEs will be tabulated by system organ class and preferred term whereby the most current implemented MedDRA dictionary will be used. In addition, summaries by severity and relationship to study drug will be done. Certain AEs, such as serious or severe, leading to premature withdrawal, will be listed and described in detail. AEs of special interest for treatments will be defined in the statistical analysis plan and analysed separately. In addition to the descriptive statistics provided, Fisher’s exact test will be used for comparisons between treatment groups.

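### Study visits end at treatment failure, so observation time depends on efficacy: crude adverse-event comparisons are tilted, and quality of life, acuity and costs after failure go unobserved

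*Protocol article*

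**What the plan says.** All references are to the protocol article.

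- **Exit rule.** Under Authorised rescue medication, if inflammation is not controlled within four weeks of rescue, or a later relapse occurs, "it will be declared treatment failure and the subject will exit the study".
- **Visit schedule.** Under Study procedures, visits continue until one of several events. Two of them are that "the subject is determined as unable to achieve complete resolution of the ocular inflammatory process by week 16" and that "the subject is determined as unable to maintain a complete resolution of the ocular inflammatory process, between weeks 16 and 52". The Study overview is consistent with this: "The duration of the treatment and follow-up will last up to 52 weeks".
- **After exit.** Table 3 has a final/early-termination (FET) visit and then only the 70-day contact, which is marked for adverse events and concomitant medication. EQ-5D, acuity and cost assessment are not marked there.
- **Adverse events.** The counting window runs from first dose to 70 days after last dose. Besides descriptive tables, Fisher's "exact test will be used for comparisons between treatment groups". No person-time measure is named.
- **Longitudinal and economic outcomes (Table 4).** EQ-5D and acuity are analysed by GEE. VFQ-25 and HADS are analysed as change to week 16 and to FET, by ANOVA. "QALYs will be calculated by the area under the curve assuming a linear evolution of EQ5D values between visits", and costs are averaged per patient in each arm.
- **Missing data.** One sentence in the Statistical analysis plan section commits to multiple imputation by chained equations.
- **Retention.** Under Recruitment, sites are to contact subjects and "educate them in the significance of research follow-up even if they decide to discontinue the study drugs".

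**The concern.** Leaving the study and failing treatment are the same event in this plan. An arm with more failures is therefore observed for less time, and the trial's own hypothesis is that the arms differ in failures. Three groups of analyses inherit this.

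1. A crude proportion with an adverse event rises with time at risk. The arm that keeps its subjects longer has more time in which to record events.
2. Exit is triggered by inflammation, which is plausibly related to EQ-5D and acuity. What happens to those measures after failure is not seen. For VFQ-25 and HADS the FET value is a 52-week change in completers and a shorter change in those who exit.
3. QALYs and costs need the whole year for every subject. The costs and quality of life that follow failure, including any change of therapy under standard care, are a large part of what an economic comparison should capture.

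Safety and cost-effectiveness are in the title and are the key secondary outcomes in Table 5.

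**Working it through.** **Planning rates (Sample size determination).** The monotherapy rate reproduces: 0.65 × (1 − 0.18 − 0.16) = 0.429, stated as 43%. The combination adds 23, read as percentage points, giving 66%. That reading fits the stated 54 per arm: a two-sided test of 66% against 43%, with twice as many monotherapy subjects, needs 55 in the combination arm by the normal formula and 54.2 by the arcsine formula. Non-response is therefore 57% against 34%, a difference of 0.23.

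**Mean weeks observed.** Assume that every non-responder exits, either all at week 16 or spread evenly over weeks 16 to 52 (mean 34). Ordinary losses are ignored.

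Mean = (response × 52) + (non-response × mean exit week)

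| Exit timing | Combination | Monotherapy | Gap |
|---|---|---|---|
| Even over 16–52 | 0.66×52 + 0.34×34 = 45.9 | 0.43×52 + 0.57×34 = 41.7 | 0.23×18 = 4.1 |
| All at week 16 | 0.66×52 + 0.34×16 = 39.8 | 0.43×52 + 0.57×16 = 31.5 | 0.23×36 = 8.3 |

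If only half of the non-responders exit, the gaps halve to 2.1 and 4.1 weeks.

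A timing closer to the protocol's methotrexate figures falls inside this range. Let 35 points of monotherapy failure exit at week 16 or week 26, let the other 22 points exit evenly over weeks 26 to 52 (mean 39), and split the combination failures in the same proportion. The means are 42.8 against 36.5 weeks (gap 6.2), or 44.9 against 40.0 (gap 4.8).

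**Adverse events with no true difference.** Assume a constant hazard, equal in all arms, and a window of exit time plus 10 weeks (70 days). For an event with risk R over the full 62 weeks, λ = −ln(1 − R)/62. A subject exiting at week t has risk 1 − exp(−λ(t + 10)).

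Example, R = 20%, all exits at week 16: λ = 0.2231/62 = 0.0036, and the risk for those who exit is 1 − exp(−0.0036 × 26) = 8.93%.
- Combination: 0.66×20 + 0.34×8.93 = 16.2%
- Monotherapy: 0.43×20 + 0.57×8.93 = 13.7%
- Ratio: 1.19

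| Full-period risk R (assumed) | Even exit: combination vs monotherapy | Week-16 exit: combination vs monotherapy | Ratio |
|---|---|---|---|
| 10% | 9.0% vs 8.4% | 8.1% vs 6.8% | 1.08–1.19 |
| 20% | 18.2% vs 16.9% | 16.2% vs 13.7% | 1.07–1.19 |
| 50% | 46.1% vs 43.4% | 41.6% vs 35.9% | 1.06–1.16 |

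With half of the non-responders exiting, the same formula gives ratios of about 1.03 to 1.08. For a near-universal event (R = 88%) with all exiting, it gives 1.03 to 1.09.

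**Quality of life, acuity and costs.** Table 3 schedules EQ-5D, VFQ-25, HADS and acuity at the relapse and FET visits, so status at failure is recorded. Nothing on these measures is scheduled after it. Any value imputed for the weeks between exit and week 52 must come from a model fitted largely to subjects still in the study, that is, those still responding on the assigned drug. For VFQ-25 and HADS, up to 34% of combination and 57% of monotherapy FET values would be earlier than week 52 (17% and 28.5% if half exit).

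**After the change.** With everyone followed to week 52, the observation gap is 0 weeks and, with equal hazards over that common period, the risk ratio is 1.00. The sample size does not move.

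**The case against.** Much of the case on the other side stands.

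- **The primary analysis is untouched.** The Mantel–Haenszel test counts every subject without the response as a non-responder, whatever the cause. A reader might infer that early exit biases the main result. It does not.
- **The largest figures are bounds.** The 8-week gap needs every non-responder to exit, and to do so at week 16. The protocol allows one rescued relapse in each period. Some non-responders, such as those above the week-52 steroid limit, would stay to the end.
- **The safety tilt is modest and its direction is not certain.** The largest gap in the table, 5.7 points, is below one standard error for 64 against 128 subjects: √(0.416×0.584/64 + 0.359×0.641/128) = 7.5 points. If the combination causes more safety exits, its exposure could be the shorter one. The tests also supplement a descriptive analysis, and an unseen SAP may add exposure-adjusted rates.
- **Truncated QALYs.** A reader might cut the QALY area at exit, assume a utility of 0.8 for everyone, and obtain a false gain of 0.23 × 0.8 × 36/52 = 0.13. The documents do not support this as an expected bias, because missing data are to be imputed. Under that same premise of equal utility, imputation would restore the missing area.
- **The retention statement.** A reader might see the Recruitment section as contradicted by the exit rule. It concerns subjects who choose to stop study drugs, whereas the exit rule concerns failure declared under the protocol. They can coexist.
- **A different model.** Replacing GEE with a likelihood-based repeated-measures model might look like a cure. It also relies on data missing at random and recovers nothing that was not collected.

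What remains is the mechanism. Imputation does not correct a Fisher's test that takes no account of time at risk, and SAP wording cannot supply post-failure data that were never collected.

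**Conclusion.** The point holds as a design weakness in the secondary safety, quality-of-life and economic comparisons.

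- **Observation time:** about 4 to 8 weeks shorter on average in the monotherapy arms if all non-responders exit, and about 2 to 4 weeks if half do. This rests on the planning rates of 43% and 66% and on exits at or after week 16.
- **Adverse events:** a spurious risk ratio of about 1.06 to 1.19 against the longer-observed arm, as an upper range. It assumes equal constant hazards, full-period risks of 10% to 50%, and exit of every non-responder for inefficacy.
- **EQ-5D, acuity, QALYs and costs:** the bias cannot be sized from the documents, because it depends on what happens after failure, which the plan does not observe. The defect is reliance on extrapolation.
- **VFQ-25 and HADS at FET:** changes over different lengths of time are pooled, in proportions that differ by arm.

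The change is worth making, but the primary conclusion does not depend on it.

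**What to change.** 1. **Adverse-event comparison.** Make exposure-adjusted incidence or time to first event the between-arm comparison, and keep the crude table beside it. This costs analysis wording only.
2. **Data collection after failure.** Leave every treatment rule as it is, but separate stopping study drug from leaving data collection. Suggested wording: *Subjects declared treatment failures stay in data collection to week 52, with EQ-5D, visual acuity, resource use and adverse events recorded at a reduced schedule of contacts.* QALYs and costs can then rest mainly on observed data, with imputation kept for ordinary losses. Report adverse events within the existing 70-day window separately from later ones, since later events may arise under other therapy.
3. **Text.** Reconcile Recruitment, Authorised rescue medication and Study procedures, so that they say what follow-up applies after declared failure and what applies after a subject's own choice to stop. State how FET values before week 52 enter the VFQ-25 and HADS analysis.

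The instruments are already in use and the sample size is unchanged. Item 2 costs site time, some patient burden, and a protocol amendment with ethics committee and agency approval.

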### Masking

For the duration of the trial, both the study subject and the Unmasked Investigators will be aware of the treatment assigned. Considering the differences between study drugs (MTX and ADA) regarding appearance, route of administration and schedule, in order to make them unaware of the medication prescribed, the use of placebo would be necessary. However, taking into account that both drugs have been proven effective in the treatment of NIU, the duration of the trial (up to 52 weeks), and the need for biweekly subcutaneous (SC) injections of one of the drugs (ADA), we consider unethical for the subject the use of placebo in the present trial.

Besides the Unmasked Investigators, the rest of participating investigators will be considered Masked Investigators (ophthalmologists performing the clinical eye exams, visual acuity examiners, Optical Coherence Tomography (OCT) operators, fundus photographers, fundus graders and administrators of subject’s questionnaires) and will not be aware of the treatment assigned to prevent bias in study outcomes.

Several steps will be taken to avoid the Masked Investigators discovering the subject assignment: they will have no part in handling or prescribing medication; subjects will be given dark bags to place and keep their medication in throughout the trial and study visits to minimise the chances of the Masked Investigators seeing the medications. Additionally, subjects will meet with the Unmasked Investigator first, before seeing any Masked Investigators, keeping any study medication in his/her office for the entire patient visit; reviewing the appearance of any AE with the subjects before seeing any Masked Investigators, and reminding the subjects not to discuss their dosing and mediation name with the Masked Investigators.

### Study procedures

Study visits will be the baseline visit, visits at weeks 1, 4, and every 4 weeks thereafter until (a) the subject is determined as unable to achieve complete resolution of the ocular inflammatory process by week 16, OR; (b) the subject is determined as unable to maintain a complete resolution of the ocular inflammatory process, between weeks 16 and 52 OR; (c) the subject completes 52 weeks of this clinical trial, OR; (d) the study is stopped due to the findings of the Data Security Monitoring Board, OR and (e) the subject meets any of the study finalisation criteria.

Informed consent has to be acquired before carrying out any study procedure, including screening tests (online supplemental file 1 contains a sample informed consent). Before baseline (when the subject is randomised), several screening visits can take place up to 14 days before that visit, in order to obtain all the required complementary tests to assess eligibility. The visit window for all scheduled visits is ±3 days through week 4 and ±7 days for all visits following the week 4 study visit. Table 3 provides an overview of the study activities.

10.1136/bmjopen-2021-051378.supp1Supplementary data

**Table 3 T3:** Study activities

Activity	Screening	Baseline	w1	w4	w8	w12	w16	w20	w24	w28	w32	w36	w40	w44	w48	FET	Relapse	Unsch.	70-day follow-up
Informed consent	X																		
Inclusion/exclusion criteria	X	X																	
Medical/surgical history	X	X																	
History of tobacco and alcohol use	X	X																	
Uveitis history	X	X																	
Vital signs/weight/height	X	X														X	(X)		
Physical exam	X	X														X	(X)		
Symptom directed physical exam			X	X	X	X	X	X	X	X	X	X	X	X	X		X		
Chest X-ray	X															X*			
Cerebral MRI†	(X)																		
TB screening	X																		
Serum pregnancy test††	X	X	X	X	X	X	X	X	X	X	X	X	X	X	X	X			
Hepatitis B/C screening	X																		
Syphilis testing (FTA)	X																		
Randomisation		X																	
Best-corrected visual acuity testing	(X)‡	(X)‡		X	X	X	X	X	X	X	X	X	X	X	X	X	X		
Tonometry	(X)‡	(X)‡		X	X	X	X	X	X	X	X	X	X	X	X	X	X		
Slit lamp exam	(X)‡	(X)‡		X	X	X	X	X	X	X	X	X	X	X	X	X	X		
Dilated indirect ophthalmoscopy	(X)‡	(X)‡		X	X	X	X	X	X	X	X	X	X	X	X	X	X		
Fundus photography	(X)‡	(X)‡					X									X	X		
Optical coherence tomography	(X)‡	(X)‡		X	X	X	X	X	X	X	X	X	X	X	X	X	X		
EuroQol-5D	(X)‡	(X)‡		X	X	X	X	X	X	X	X	X	X	X	X	X	X		
Visual Functioning Questionnaire-25	(X)‡	(X)‡					X									X	X		
Hospital Anxiety and Depression Scale	(X)‡	(X)‡					X									X	X		
Haematology/chemistry	X	(X)§	X	X	X	X	X		X		X		X		X	X	(X)		
Monitor adverse events		(X)	X	X	X	X	X	X	X	X	X	X	X	X	X	X	X	X	X
Monitor concomitant medication	X	X	X	X	X	X	X	X	X	X	X	X	X	X	X	X	X	X	X
Review of patient diary			X	X	X	X	X	X	X	X	X	X	X	X	X	X	(X)		
Perform drug accountability			X	X	X	X	X	X	X	X	X	X	X	X	X	X	(X)		
Assessment of direct and indirect costs			X	X	X	X	X	X	X	X	X	X	X	X	X	X	(X)		
Dispense study drugs		X	X	X	X	X	X	X	X	X	X	X	X	X	X		(X)		
Proteomic blood sample	(X)¶	(X)¶					X									X	X		
Pharmacogenetic blood sample	(X)¶	(X)¶																	
Adalimumab levels and antiadalimumab antibodies	(X)¶	(X)¶					X**			X**						X**	X**		

*Chest X-ray will be performed at the 52 weeks/early termination visit in case the patient had a positive TB test at baseline.

†Cerebral MRI will be performed only in those subjects with intermediate uveitis or signs of intermediate uveitis.

‡Values from the baseline visit or from a screening visit up to 14 days before the baseline visit will be used as the values from the baseline visit.

§Total blood count, renal and liver function test from up to 4 weeks before the baseline visit will the required before entering the study.

¶Blood sample will be drawn after signature of the informed consent, as soon as possible, ideally before start of oral GCs.

**Blood samples for the antiadalimumab antibodies will be drawn the week before visits 16, 28, 52. Early termination and relapse visits, up to 24 hours before the patient is scheduled to receive the ADA dosage, and always before the medication is taken.

††Only in women in childbearing

FET, final (w52)/early termination visit; ISD, Immunosuppressive Drug; NYHA, New York Heart Association; PPD, Purified protein derivative; TNF, Tumor Necrosis Factor; Unsch, unscheduled visit; w, week.

After the trial, all patients will return to standard care and will be able to continue with their assigned study medication.

